## 2 Materials and methods

### 2.1 Study design

This is a prospective, single-center, double-blind, randomized, propofol-controlled, non-inferiority trial, which will be carried out at Tongren Hospital, School of Medicine, Shanghai Jiao Tong University, Shanghai, China. This trial protocol was approved by the Medical Ethics Committee of Tongren Hospital, School of Medicine, Shanghai Jiao Tong University (Approval No. 2023–035) and registered at the ClinicalTrials.gov (Identifier: NCT06251999) on 21 January 2024. The implementation of this trial will be in accordance with the Declaration of Helsinki. The protocol follows the guidelines of Standard Protocol Items: Recommendations for Interventional Trials (SPIRIT) (Chan et al., 2013).

### 2.2 Participants

An independent investigator, who is not involved in the subsequent study, screens the admission records for recruitment of eligible patients. Written informed consent will be obtained from the patient or their representative before each patient performed any procedure. At any time during this study, patients can withdraw their consent without any consequence. A total of 256 eligible patients aged 65 years or older, who are scheduled for same-day bidirectional endoscopy under sedation, will be randomly allocated to either fospropofol group or propofol group at a ratio of 1:1 (n = 128 in each group). The flow chart of this study is presented in Figure 1.

**FIGURE 1 F1:**
[figure not shown]
The flow chart of this study.

#### 2.2.1 Inclusion criteria

The inclusion criteria are as follows.

1) 65 years or older; 2) American Society of Anesthesiologists (ASA) physical status I to III; 3) body mass index (BMI) 18–30 kg/m^2^, and 4) scheduled for same-day bidirectional endoscopy under sedation.

#### 2.2.2 Exclusion criteria

The exclusion criteria are as follows.

1) severe cardiovascular, pulmonary, renal, or hepatic disease; 2) previous hypotension (systolic blood pressure ≤90 mmHg), bradycardia (heart rate <50 beats/min), or hypoxemia (SpO2 <90%); 3) neurocognitive or psychiatric disorders; 4) contraindications to gastroscopy (gastric retention, long-term aspirin administration, etc.); 5) hypersensitivity to study medications; 6) drug or alcohol abuse; 7) definite upper respiratory tract infection; or 8) refusal to participation.

### 2.3 Randomization and blinding

Eligible patients will be randomly assigned to either the fospropofol group or the propofol group at a 1:1 ratio using a computer-generated sequence. Group assignments are placed into opaque, sealed, consecutively numbered envelopes by staff who is not involved in the trial. The envelopes will be opened just before the gastrointestinal endoscopy by a certified registered anesthetist who also prepares the drugs in coded syringes according to the order number indicating the group of assignment, and she/he is not associated with patient management or data collection and analysis. Patients, endoscopists, anesthesiologist, peri-procedural care providers, and outcome observers are blinded to group assignment until the end of final analysis.

### 2.4 Study procedures

On the day of the gastrointestinal endoscopy, the patient will be given an intravenous infusion channel in the waiting room. After admission to the endoscopy room, all patients will be placed in a left lateral decubitus position and monitored according to our hospital standards including real-time monitoring of electrocardiogram (ECG), peripheral blood oxygen saturation (SpO_2_), end-tidal carbon dioxide (EtCO_2_), non-invasive blood pressure (NIBP), and respiratory rate (RespR) measured every 5 min. Supplemental oxygen will be given via a transparent nasal cannula at 5 L/min throughout the procedure.

The patients will receive intravenous sedation regimen according to previous literature (Gan et al., 2010; Bergese et al., 2013), administered by the same anesthesiologist unaware of patient allocation group. All patients receive analgesic pre-treatment with sufentanil 5 μg via an intravenous infusion channel. It is recommended that patients receive only one additional dose of sufentanil 2.5 μg if the patient continues to experience pain during the procedure; however, additional doses of sufentanil (given at least 10 min after the previous dose) are allowed. After 2 min, an initial bolus dose of fospropofol 6.5 mg/kg or 1.5 mg/kg propofol and supplemental doses of fospropofol 1.6 mg/kg or 0.5 mg/kg propofol will be administered as needed to achieve a Modified Observer’s Assessment of Alertness/Sedation (MOAA/S) score ≤4 according to random group, allowing the physician to start the procedure. The bidirectional endoscopic procedures will be performed by experienced professional endoscopic teams in an esophagogastroduodenoscopy-colonoscopy sequence (Cao et al., 2017; Laoveeravat et al., 2020). This dosing schedule is also used to maintain adequate sedation levels during the procedure if the patient has a MOAA/S score ≥4 and shows purposeful movement. As deep levels of sedation (MOAA/S scores of 0 and 1) may be associated with an increased risk of respiratory compromise, additional doses of fospropofol or propofol are not administered to patients who had a MOAA/S score below four or who is not show purposeful movement during the sedation phase. If the patient sufferes from respiratory depression (SpO_2_ <90% for >10 s), the essential respiratory support such as chin/jaw lifting or assisted mask ventilation will be provided immediately until SpO_2_ returns to normal. In case of hypotension (MAP <70 mmHg or the decline reached 20% of the basal value) lasting more than 1 min, rehydration and intravenous injection of 50 µg phenylephrine will be administered. If bradycardia (HR < 50 beats/min) occurred, 0.5 mg atropine will be given intravenously.

Upon the completion of endoscopic procedures, the anesthesiologist will assess the patient’s consciousness and hemodynamic data, and then transfer the patient to the post-anesthesia care unit (PACU) for postoperative care. All patients will stay in the recovery room for at least 30 min. The modified Aldrete Score is used to assess the overall recovery of patients. Patients are allowed to be discharged if a modified Aldrete score of nine or more is identified (Laoveeravat et al., 2020). The initial dose of sedative medication and the number and dose of supplemental doses given will be recorded, and the total amount of sedative medication administered to the patient is calculated. The schedules of patient enrollment, study interventions, and outcome assessments will be in accordance with the SPIRIT statement (Table 1).

**TABLE 1 T1:** Schedule of enrollment, interventions, and assessments.

Timepoint	Study period						
	Enrollment	Allocation	Post-allocation				Close-out
	Anesthesia clinic visit	Prior to sedation	During sedation	Sedation emergence	15 min in recovery room	30 min in recovery room	Hispital discharge
Enrollment							
Eligibility criteria	×						
Exclusion criteria	×						
Written informed consent	×						
Demographic data	×						
Baseline characteristics	×						
Randomization		×					
Allocation		×					
Interventions							
Propofol		×					
Fospropofol		×					
Assessments							
The success rate				×			
Time to successful induction			×				
Time to being fully alert				×			
Time to discharge							×
Total dosage of experimental drugs				×			
Total dosage of sufentanil				×			
Total times of top-up dosing				×			
Top-up dosing times of sufentanil				×			
Endoscopist satisfaction			×				
Patient satisfaction							×
Cough reflex			×				
Gag reflexes			×				
Body movement			×				
Muscular tremor			×				
Injection pain			×				
Nausea and vomiting				×	×	×	×
Paresthesia				×	×	×	×
Pruritus				×	×	×	×
Apnea			×	×	×	×	×
Hypoxia events			×	×	×	×	×
Hypotension events			×	×	×	×	×
Bradycardia			×	×	×	×	×

According to SPIRIT, 2013 statement of defining standard protocol items for clinical trials (Chan et al., 2013).

### 2.5 Efficacy assessments

#### 2.5.1 Primary efficacy outcomes

The success rate of the gastrointestinal endoscopy will be assessed according to the following criteria (Luo et al., 2022; Zhong et al., 2023): (1) completion of the gastrointestinal endoscopy; (2) no need for rescue sedative/anesthetic, which means the top-up doses of the experimental drugs will be administered no more than five times within any 15-min window from the initial administration to the end of the procedure.

#### 2.5.2 Secondary efficacy outcomes

(1) Time to successful induction of anesthesia/sedation, defined as the time from the start of drug administration to the achievement of a MOAA/S score ≤1; (2) time to being fully alert, defined as the time from gastrointestinal endoscopy extraction or/and the time from the last drug administration to a MOAA/S score of five on three consecutive measurements; (3) time to discharge, defined as the time from the gastrointestinal endoscopy extraction or/and the time from the last drug administration to the initial occurrence of three consecutive Aldrete measurements of 9; (4) the top-up frequency and dosage of the study medications and sufentanil; (5) anesthesia/sedation satisfaction scores of the patients and endoscopists collected when the patients are ready for discharge.

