### 2.10 Data management and statistical analysis

Statistical analysis in this trial will be performed using SPSS 25 (SPSS Inc., Chicago, Illinois, United States). Continuous variables are presented as the mean ± standard deviation (SD) or median with the upper and lower quartiles, whereas categorical variables are presented as frequencies and percentages. A P-value <0.05 is considered statistically significant. For the primary efficacy outcome, the difference in gastrointestinal endoscopy success rate between fospropofol and propofol groups and the corresponding two-sided 95% confidence intervals (CIs) will be calculated. Non-inferiority between fospropofol and propofol is concluded if the lower limit of the two-sided 95% CI of the difference in success rate between fospropofol and propofol groups exceeds the non-inferiority margin (−8%). The success rates of gastrointestinal endoscopy will be compared between the fospropofol and propofol groups using the Chi-square test or Fisher’s exact test. The Shapiro-Wilk’s test will be used to assess the data distribution. For comparison of secondary efficacy outcomes, the Cochran–Mantel–Haenszel (CMH) test or Fisher’s exact test will be used to compare the categorical variables between two groups, while a t-test (normal distribution) or Mann-Whitney U test (non-normal distribution) is used to compare continuous variables, as appropriate. The incidence of AEs and drug-related AEs between the two groups will be compared using a chi-square test or Fisher’s exact test. In addition, the further interaction analysis across the subgroups, including age (65–79 years vs. ≥ 80 years), history of cardiovascular, renal, hepatic, and pulmonary diseases (yes vs. no), as well as interventional therapeutic endoscopic procedures (yes vs. no), will be carried out using a logistic regression model to adjust the study outcomes for above-mentioned potential confounding factors. All randomly assigned patients who receive at least one dose of the study medication will be included in the full analysis set (FAS) according to the intention-to-treat (ITT) principle, and at least one evaluable efficacy outcome is used for the analysis of all efficacy outcomes and baseline characteristics of patients. The safety set (SS), which includes all patients based on the “as treated” principle, will be used for the analysis of safety outcomes. Since the anticipated protocol violation will be uncommon and missing data will be supposed to be missing at random, the interim analysis or imputation for missing data are not performed in this trial.

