Fospropofol is a water-soluble, phosphate ester prodrug, which can be metabolized by alkaline phosphatases to release liberated propofol after intravenous administration (Garnock-Jones and Scott, 2010). The released propofol from fospropofol binds to the γ-aminobutyric acid (GABA) receptor and thereby potentiates GABA-inhibitory synaptic currents to induce sedative effects (Garnock-Jones and Scott, 2010). A study of its pharmacodynamic/pharmacokinetic relationship in 12 healthy volunteers found that an intravenous bolus 10 mg/kg dose of fospropofola achieved propofol plasma maximum concentration of 2.2 mg/mLafter 8 (range 4–13) minutes, and reached the minimum mean MOAA/S score of 1.2 after 7 (1–15) minutes. Participants in this study completely recovered from sedation after 21–45 min following fospropofol administration (Bengalorkar et al., 2011). As a new sedative, fospropofol is expected to have the same sedative efficacy as propofol in elderly patients undergoing same-day bidirectional endoscopy, with a lower incidence of adverse reactions caused by hemodynamic and respiratory depression than that of propofol. On bassi of a phase II dose-response trial in patients undergoing colonoscopy, fospropofol 6.5 mg/kg was determined as the ideal dose, as no recorded episodes of deep sedation occurred during procedures under this dose (Cohen, 2008). In addition, both physicians and patients mostly preferred for fospropofol 6.5 mg/kg over the other doses (Cohen, 2008). In two clinical trials, fospropofol was shown to be safe and well tolerated at an initial dose of 6.5 mg/kg intravenously with supplemental doses as moderate sedation for elderly, obese, and high-risk patients in minor surgical procedures (Gan et al., 2010; Bergese et al., 2013). Fospropofol disodium for injection is a prodrug that is metabolized into propofol to produce a general anesthetic effect when administered intravenously. A phase 3 trial demonstrated that fospropofol disodium was not inferior to propofol for general anesthesia induction in American Society of Anesthesiologists (ASA) physical status I-II adult patients undergoing elective surgery and reduced the incidence of pain at the injection site (Wu et al., 2021). In addition, fospropofol’s slower onset should have less impact on patient’s hemodynamics compared to propfol, although it may potentially slow patient recovery (Gan et al., 2010). In clinical conditions where a more prolonged effect is desired and immediate onset of action is less important, fospropofol may have advantages over propofol. A pilot study has shown that fospropofol, administered in either an infusion/bolus or infusion-only regimen, is tolerable and effective for the short-term induction and maintenance of sedation in mechanically ventilated intensive care unit patients (Candiotti et al., 2011). These findings have prompted to exploration of fospropofol in providing sedation for elderly patients undergoing same-day bidirectional endoscopic procedures. However, the role of fospropofol sedation for same-day bidirectional endoscopy in elderly patients has not been fully determined. To our knowledge, this will be the first randomized controlled trial to assess the efficacy and safety of fospropofol sedation for same-day bidirectional endoscopy in elderly patients. In our patients, an initial bolus dose of fospropofol 6.5 mg/kg in combination with sufentanil 5 μg will be used for sedation induction, followed by supplemental doses of fospropofol 1.6 mg/kg as needed to achieve target sedation levels. This strategy will minimize the risk of oversedation and associated complications. Moreover, several confounding factors, which can influence the study outcomes, must be appropriately managed in this study to ensure that the reliable conclusions are obtaine. Subgroup analyses of the efficacy and safety assessments will be performed on basis of age, interventional therapeutic endoscopic procedures, history of cardiovascular, renal, hepatic, and pulmonary diseases.

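### Time to successful induction ends at MOAA/S ≤1, but the dosing rule starts the procedure at MOAA/S ≤4, so patients sedated as planned can have no value for this secondary outcome

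*Protocol article*

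**What the plan says.** Section 2.5.2 gives as the first secondary efficacy outcome: "Time to successful induction of anesthesia/sedation, defined as the time from the start of drug administration to the achievement of a MOAA/S score ≤1".

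Section 2.4 sets the dosing rule. The bolus and supplemental doses are given to reach a MOAA/S "score ≤4 according to random group, allowing the physician to start the procedure". During the procedure the same schedule applies "if the patient has a MOAA/S score ≥4 and shows purposeful movement", while "additional doses of fospropofol or propofol are not administered to patients who had a MOAA/S score below four". The reason given there is that scores 0 and 1 are deep sedation and may bring respiratory compromise.

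Section 3 (Discussion) supports the fospropofol dose of 6.5 mg/kg with a cited phase II dose-response trial in colonoscopy, in which "no recorded episodes of deep sedation occurred during procedures under this dose". It also reports that 12 healthy volunteers given 10 mg/kg had a lowest mean score of 1.2. It gives no depth-of-sedation figure for propofol 1.5 mg/kg.

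For continuous secondary outcomes, section 2.10 states that "a t-test (normal distribution) or Mann-Whitney U test (non-normal distribution) is used to compare continuous variables". It assumes that missing data are missing at random and rules out imputation.

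**The concern.** The outcome ends at a depth that the dosing rule does not aim for, does not top up towards, and names as a risk. A patient who reaches 4, 3 or 2 and is scoped as intended never meets the definition and has no induction time. A patient who drifts to ≤1 after a top-up during the procedure gets a time that ends after endoscopy has started, which is not an induction time in the ordinary sense.

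If patients without a time simply drop out, the comparison is between those in each arm who became deeply sedated. Membership of that subset is an effect of the drug, so randomisation no longer protects the comparison. The missing-at-random assumption does not fit either, because the value is absent owing to the response itself. This is the first-listed secondary outcome, and it bears directly on the slower onset that the article expects of fospropofol.

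**Working it through.** **Plan's own figures.** The article gives no figure for this outcome. Its sample size concerns the primary outcome only, and it reproduces: n per arm = (1.960 + 0.842)² × 2 × 0.95 × 0.05 / 0.08² = 116.5, rounded up to 117, so 234 in total as stated in section 2.9. Nothing in it depends on MOAA/S ≤1.

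**Step 1: thresholds side by side.**

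| Purpose | Section | MOAA/S |
|---|---|---|
| Procedure may start | 2.4 | ≤4 |
| Top-up given | 2.4 | ≥4 with purposeful movement |
| Top-up withheld | 2.4 | <4, or no purposeful movement |
| Described as deep sedation with respiratory risk | 2.4 | 0 and 1 |
| Still sedated (prolonged sedation) | 2.6 | ≤4 |
| Induction successful | 2.5.2 | ≤1 |

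Scores of 4, 3 and 2 permit the start of the procedure but do not count as successful induction. No other section reconciles the two levels.

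**Step 2: share of patients without an induction time.** Let pF and pP be the proportions reaching ≤1 on fospropofol and propofol. With 128 per arm, the overall share without a value is 1 − (pF + pP)/2. Neither proportion is in the article, so the rates below are assumptions. The row pF = 0 is the literal reading of the cited phase II result.

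| pF (patients of 128) | pP = 100% | pP = 50% | pP = 10% |
|---|---|---|---|
| 0% (0) | 50% | 75% | 95% |
| 10% (13) | 45% | 70% | 90% |
| 30% (38) | 35% | 60% | 80% |
| 50% (64) | 25% | 50% | 70% |

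The range is 25% to 95%. The overall share does not show how unequal the arms are. A figure of 50% arises from 0 against 128 patients with a value (pF = 0%, pP = 100%), from 13 against 115 (10%, 90%), and from 64 against 64 (50%, 50%).

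**Step 3: what the volunteer figure shows.** MOAA/S takes whole numbers. Assuming all 12 volunteers were scored, a mean of 1.2 is a sum of about 14 (14/12 = 1.17). If k volunteers scored 2 or more, the sum is at least 2k, so k is at most 7. At least 5 of 12 (42%) were therefore at ≤1. At 10 mg/kg, a dose 10/6.5 = 1.54 times the one used here, the level was reached by a substantial fraction. The figure does not show that ≤1 is rare, and it does not settle the rate at 6.5 mg/kg.

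**The case against.** The strongest reply is that a depth that is not targeted may still be reached. A single weight-based bolus can overshoot ≤4. The patients are 65 or older, a group the Introduction calls more sensitive to sedatives, and all receive sufentanil first. The phase II statement comes from colonoscopy alone, and the article does not show its definition of deep sedation, its co-medication or its age range. This stands. A reader might infer that most patients will lack an induction time, or that the fospropofol arm will be nearly empty. The article does not support either as a prediction: they lie at one end of an assumed range.

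A reader might also infer that values will be missing for different reasons in the two arms. That has no support. The same rule governs both arms and the reason is the same, namely that ≤1 was not reached. Only the rate may differ.

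It can further be said that section 2.10 names generic tests and nowhere excludes non-attainers, that their handling may be left to an analysis plan not shown here, and that ranking them last is itself a Mann-Whitney analysis. This is fair, and the consequence for the analysis is therefore conditional. But an analysis plan could only manage the non-attainers. It would not remove the conflict between sections 2.4 and 2.5.2.

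Finally, the slip may lie in section 2.4, where a score of 4 both permits the start and, with purposeful movement, calls for a top-up. That is a reason to ask for reconciliation without presuming which level is meant.

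**Conclusion.** The contradiction is real and the article does not resolve it. As written, an unknown and possibly unequal share of each arm will have no induction time. Under the assumed rates of 0–50% for fospropofol and 10–100% for propofol, the overall share is 25% to 95%. That range rests wholly on those assumptions. A difference between arms is plausible, because the article describes slower onset and no deep sedation at the fospropofol dose used, but it cannot be quantified.

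If non-attainers are left out, the onset comparison is between subsets selected after randomisation and cannot be read as an effect of the drug in all dosed patients. This should be fixed, but it is confined to one secondary outcome. The primary outcome uses procedure completion and the top-up count, so it, the non-inferiority conclusion and the sample size are untouched.

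**What to change.** - **Section 2.5.2 (one sentence).** The investigators should reconcile sections 2.4 and 2.5.2 before unblinding, so that induction time ends at the same sedation level that the dosing rule uses to start the procedure. Which level that is remains their clinical decision.
- **Section 2.10 (one sentence).** State one analysis covering all dosed patients: either a time-to-event comparison with non-attainers censored, or a Mann-Whitney test with non-attainers ranked last. Report the proportion in each arm that reaches MOAA/S ≤1.

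Fixing both before unblinding matters because a threshold or a rule for non-attainers chosen afterwards could be driven by the results. The cost is small. MOAA/S must already be scored to apply the dosing rule, though Table 1 does not list it as a separate recorded item, so the investigators should check that the case report form holds each score with its time.

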### 2.6 Safety assessments

Safety will be assessed by the rate of occurrence of adverse events (AEs). AEs are evaluated for frequency, severity, association to the study drug, relationship to procedure, and outcome. The severity of AEs is graded based on the Common Terminology Criteria for Adverse Events (CTCAEs, version 5.0). The causal relationship of an AE to the investigated drug (fospropofol or propofol) will be assessed by the investigator using the classifications shown in Table 2 according to previous literature (Luo et al., 2022). AEs are considered severe if they affects a patient’s daily function or threatens their life. If cough reflex, gag reflexes, body movement, muscular tremor, pain on injection, or other reactions caused by operation irritation will be observed in patients, they are recorded as operational reactions of gastrointestinal endoscopy. Sedation-related AEs, including hypoxia, hypotension, bradycardia, and prolonged sedation, are evaluated from the time of administration of bolus doses of the study drug until the discharge of patients. Hypoxia is defined as pulse oxygen saturation (SpO_2_) < 90% lasting for >30 s; hypotension is defined as systolic blood pressure (SBP) < 90 mmHg or a decrease of 20% from baseline lasting for >2 min; bradycardia is defined as heart rate (HR) < 50 beats/min and lasting for >2 min. Prolonged sedation is defined as a MOAA/S score ≤4 for more than 30 min after the end of the colonoscopy.

**TABLE 2 T2:** Classification of AEs potentially associated with fospropofol or propofol.

Indicator	Definitely related	Probably related	Possibly related	Possibly not related	Not related
Reasonable time sequence	Yes	Yes	Yes	Yes	Yes
Belongs to the type of reaction known to be produced by the study drug	Yes	Yes	Yes	No	No
Reaction may be improved after discontinuation of the study drug	Yes	Yes	Yes or No	Yes or No	Yes or No
Reaction may re-occur with medication	Yes	?	?	?	No
There is another explanation for the reaction	No	No	Yes	Yes	Yes

